### Control arm

Participants randomised to the control arm will not be offered any PM+ but will be able to access all usual care and support offered by the participating NGOs. To control for the weekly contact that the active arms will receive, participants randomised to the control arm will be invited by the interviewing researcher to attend a local AS&R NGO of their choice. They will be put in contact with other AS&Rs from similar backgrounds and encouraged to meet together on a weekly basis for 5 weeks.

### Participant identification

Potential participants will be identified primarily through NGOs and primary care teams, all designated as Participant Information Agencies (PIAs). PIAs will be provided with a short summary of the study including the main inclusion and exclusion criteria. They will be asked to display posters and leaflets and discuss the study opportunistically with AS&Rs who access the services. All participant-facing documentation will have the necessary approvals from a Research Ethics Committee (REC).

Potential participants will be made known to the research team via one of the following methods:
By them contacting the research team directly via telephone or emailBy agreeing to their details being given to the research team (via a participant recommendation form, completed by the PIA with the AS&R, and returned to the research team by the PIA)By attending a researcher-attended drop-in session at collaborating NGOs on a specific date/time, advertised by posters/leaflets/verbally

Following identification of a potential participant, a postdoctoral researcher based in the University of Liverpool, who is trained in the PROSPER trial techniques and in discussion about informed consent, will arrange a meeting to give more information about the trial.

### Informed consent

The researcher will contact the potential participant to arrange an individual face-to-face meeting. This meeting will be arranged at the convenience of the AS&R where possible and can be attended by an interpreter if required. The meeting will last between 1 and 2 h. It will take place at a convenient location which could include one of the NGO centres, a community centre, a counselling centre, NHS premises and the University of Liverpool.

Objectives, risks and inconveniences of the trial and the conditions under which it is to be conducted will be provided by the researcher. All potential participants will be given the opportunity to ask any questions that may arise, will have the opportunity to discuss the study with others and be given time to consider the information prior to agreeing to participate. It will be made clear to the participant that an eligibility assessment will be conducted once consent is given and that if the participant is found to be ineligible for any reason that they will be unable to participate.

The potential participant will be asked to read and review the Participant Information Sheet (PISC), which is available in English and the study languages of Farsi, Urdu and Arabic. Upon reviewing the document, the researcher will explain the research study to the potential participant. The PISC and the discussion with the participant will emphasise that participation in the trial is voluntary and that the participant may withdraw from the trial at any time and for any reason. Participants will also be asked for permission for the research team to share relevant data with people from the Universities taking part in the research or from regulatory authorities, where relevant. This trial does not involve collecting biological specimens for storage. The researcher is aware of the sensitive nature of the research topic and will minimise any distress caused to potential participants as a result of the discussions.

If the asylum seeker or refugee decides that they would like to participate, they will then personally sign and date the informed consent document. The document will then be signed and dated by the person obtaining consent. A copy of the informed consent document will be given to the potential participant for their records. The original document will be maintained by the research team separate from any personal identifiable information collected for any participants. A further copy will be sent to the Liverpool Clinical Trial Centre (LCTC) via secure methods if the participant is eligible for full trial participation; this will be sent separately from any participant data subsequently collected. The PISC (which includes informed consent documentation) is available from the corresponding author on request.

If the potential participant requires more time to consider involvement in the trial a further meeting can be arranged at the discretion of the researcher. If the individual does not wish to take part, their reason for not providing consent will be recorded on the PROSPER Screening Log. Once consent has been given the participant may, without being subject to any resulting detriment, withdraw from the trial at any time by revoking the informed consent.

### Eligibility and baseline assessments

Once written informed consent has been obtained, the potential participant can be assessed for eligibility, as per the criteria detailed above.

Eligibility assessment will follow a staged process. The researcher will review responses at the end of each stage and, if the potential participant is found to be ineligible, they will be informed of this and there will be no requirement for completion of the next stage.

Firstly, through discussion with the potential participant, the researcher will answer socio-demographic questions. The researcher will then assess the following exclusion criteria: complex mental disorder (bipolar disorder/manic depression, or schizophrenia); cognitive impairment (moderate/severe intellectual disability, any dementia); substance misuse; currently receiving a formal psychological therapy. If the potential participant remains eligible, they will be asked to self-complete the HADS, WHODAS and PHQ-9 questionnaires within the Eligibility Questionnaire Booklet. These questionnaires are all available in English, Arabic, Farsi and Urdu. The researcher will review the completed PHQ-9 questionnaire to assess whether the potential participant is at imminent risk of suicide. If there are any concerns regarding suicide risk, the researcher will follow the procedure outlined in the Suicidal Ideation Guidance Document.

If the potential participant is eligible following this process, the researcher will conduct the baseline assessments outlined in the following section. This will allow consistency for outcome measurement completion, and also reduce the need for attendance at additional meetings. If the researcher has any concerns or uncertainties from the non-clinical eligibility assessment above, they will contact the chief investigator (CI) or nominated deputy to discuss the case.

AS&Rs who are assessed as ineligible can be reconsidered for participation at a later date if circumstances change, e.g. if they are able to register with a GP. If this is more than 2 weeks after consent was obtained, the consent process will be repeated.

Following the completion of the eligibility assessment, the researcher will ask the eligible participant to self-complete the Baseline Questionnaire Booklet, which incorporates the remaining baseline assessments: the WHO-5, PSYCHLOPS and PCL-5 questionnaires. The CSRI Form, which has been adapted for PROSPER, will be completed by the researcher through discussion with the participant.

For a potential participant who completes the eligibility assessment process and is deemed eligible to participate in PROSPER Pilot, but where there was concern or uncertainty that necessitated the researcher contacting the CI or nominated deputy, the CI or nominated deputy will review the information provided by the participant to verify eligibility for trial participation and complete the Eligibility and Baseline CRF before randomisation occurs.

### Randomisation

Participants will be randomised using a secure, web-based randomisation programme. Randomisation lists will be generated in a 1:1:1 ratio, to individual PM+, group PM+ and control, using block randomisation with random variable block sizes.

The randomisation list will be generated by a statistician independent to the PROSPER trial. Given the open nature of the trial, it will not be possible to blind researchers, trial participants, care providers, outcome assessors or data analysts to the intervention arm to which participants are assigned.

The researcher will update the PROSPER Screening Log when a participant has been randomised. The researcher will be responsible for notifying the participant of their allocation. In the event that a participant is randomised to individual or group PM+, the researcher will inform the PSS Lead. Intervention delivery will be coordinated by PSS in collaboration with the participant and their lay therapist. The research team will notify the participant’s GP by letter of their enrolment into the trial and to what treatment arm they have been allocated.

### Assessments and follow-up

All assessments and follow-up will be conducted in line with the schedule of assessments summarised in Table 4.

**Table 4 Tab4:** Schedule of assessments

	Screening and baseline	Randomisation	13-week follow-up	26-week follow-up
**Time point (weeks)**	0	0	13 ± 2	26 ± 2
**Procedures:**				
Consent, eligibility screening and confirmation				
Written and Informed consent	X			
Assess eligibility	X			
Confirm eligibility	X			
Randomisation		X		
Confirm consent		X	X	X
Data collection				
HADS	X		X	X
WHODAS	X		X	X
PHQ-9	X		X	X
PSYCHLOPS	X		X	X
PCL-5	X		X	X
WHO-5	X		X	X
CSRI	X		X	X
Adverse events				
Assessment of AEs	X		X	X

Abbreviations: *AEs* adverse events, *CSRI* Client Service Receipt Inventory*, HADS* Hospital Anxiety and Depression Scale, *PCL-5* Post-traumatic Stress Disorder Checklist for DSM-5*, PHQ-9* 9-item Patient Health Questionnaire*, PSYCHLOPS* Psychological Profiles Instrument,*, WHO-5* World Health Organisation Five Wellbeing Index, *WHODAS* World Health Organisation Disability Assessment Schedule

In the case of premature discontinuation/withdrawal, there are no additional assessments for participants.

All specified outcomes will be measured at 13 (± 2) and 26 (± 2) weeks post baseline; 13 weeks will be the primary end point: this is consistent with previous trials [28]. It allows time for intervention delivery and often may correspond to the timings of Home Office decisions on leave to remain for asylum seekers.

#### Follow-up visit: 1–13-week follow-up

This is expected to be a face-to-face appointment at 13 weeks ± 2 weeks from baseline, and include:
Verbal confirmation of continued consentThe participant will complete the following questionnaires within the Follow-up Questionnaire Booklet: HADS, WHODAS, PHQ-9, WHO-5, PSYCHLOPS, PCL-5If suicidal ideation is disclosed or suspected, the researcher will follow the steps outlined in the Suicidal Ideation Guidance documentRecording of any adverse event informationResearcher-led completion of the adapted CSRICompletion of Follow-up CRF

#### Follow-up visit: 2–26-week follow-up

This is expected to be a face-to-face appointment at 26 weeks ± 2 weeks from baseline, and to follow the same process as the follow-up appointment at 13 weeks.

All follow-up appointments will be coordinated and conducted by the trained researcher. They will conduct a preliminary review of the data collected to screen for missing data or any responses that may need further follow-up or clinical discussion. Follow-up appointments are expected to take around 1 h which should allow for completion of all data collection and review of any adverse events. If a face-to-face appointment cannot be arranged during the follow-up window then the visit can be conducted by telephone if possible. If the research team is unable to make arrangements to administer the assessments, the option of the participant self-completing the assessments and returning them by post will be explored. It is expected that participant responses will be completed during the appropriate visit window.

The PROSPER Pilot study design is summarised in Fig. 1.

**Fig. 1 Fig1:**
[figure not shown]
Schematic of the study design

### Statistical considerations

A detailed statistical analysis plan (SAP) will be developed prior to the first comparative monitoring report to be presented to the Independent Data and Safety Monitoring Committee (IDSMC). The main features of these planned statistical analyses, which refer specifically to the PROSPER Pilot, are detailed below.

The aim is to recruit 105 participants, 35 to each of three arms – individual PM+, group PM+ and control. Individual sessions will be offered as gender- and language-specific, i.e. the lay therapist and the study participant will be the same gender and will be comfortable in a common language. At least four groups will be offered for the group intervention, each with up to eight or nine participants, each gender-specific, i.e. participants will all be the same gender and at least one of the lay therapists will be of the same gender as the participants.

The sample size needs to be sufficient to estimate retention levels in a definitive trial. With an expectation of 80% retention, samples of 35 participants for each of the individual, group and control arm will provide an accurate estimate of retention ± 13% (67 to 93%).

Retention rates will be assessed in each arm separately, as there may be systematic differences between them; for example, those randomised to the control arm may be less likely to remain engaged than those randomised to the individual or group arms, while those randomised to the group arm may be demotivated if faced with a lengthy wait for their group to begin.

No formal interim analysis is planned as this is a pilot study and there are no anticipated problems that are detrimental to the participant. There will be monitoring by the IDMSC, who will provide a recommendation to the Trial Steering Committee (TSC) on the continuation of the trial.

Analysis will be by the intention-to-treat principle as far as is practically possible. All analyses will be descriptive, focussed on assessing the criteria for deciding whether to progress to a full trial. All estimates of proportions will be presented with 95% confidence intervals. Rates of recruitment and attrition will be presented both for lay therapists and trial participants, along with the proportion of PM+ interventions which are successfully delivered per protocol. The proportion of missing data in the proposed trial outcome measures will be assessed.

Preliminary exploration of estimates of efficacy will involve a group-wise comparison of the primary outcome: severity of combined anxiety and depressive symptoms at 13 weeks post baseline measured using the HADS.

Socio-demographic data, and use of services and supports will be captured by the adapted Client Service Receipt Inventory [37]. This data can be used for a wide range of applications, including estimating the costs of service receipt and societal costs.

No formal testing of intervention effect will be carried out, but estimates of between-group differences between the test groups and the control in outcome measures will be presented, with 95% confidence intervals, to assess whether a clinically important improvement in outcome would be plausible in a full trial. The effect of clustering by intervention provider on outcomes in the two PM+ groups will be investigated, to inform design of a full trial with a partially nested design.

### Process evaluation and feasibility assessment

Relevance and acceptability of proposed outcomes will be tested, with a view to their incorporation or refinement for a definitive trial. These will include:
Effectiveness of PM+, based on the primary outcome of combined HADS scoresCost-effectiveness of PM+ from a NHS perspective, based on the primary outcome of combined HADS scores [40, 41]Cost benefit from a societal perspective, given that costs and potential benefits will extend beyond the NHS to local government and voluntary sectors [42–44]Impact on health inequalities using the NIHR CLAHRC NWC Health Inequalities Assessment Toolkit (www.hiat.org.uk): first, within AS&R communities in relation to age, gender, nationality, education, prior occupation and asylum status; and second, between AS&Rs and national populations, comparing mental health status (anxiety, depression PTSD and wellbeing) with UK population norms, with reference to published psychiatric morbidity data [45]

The feasibility of the 13- and 26-week time points will be assessed, with specific reference to rates of participant attrition.

Researchers will undertake a systems-based *process evaluation* [46], beginning 3 months into the PROSPER Pilot, to: understand service provider and participant experiences and perspectives on acceptability, efficiency, implementation and development of PM+; understand service-users’ perceptions and experiences of accessing and participating in PM+; explore how PM+ fits into existing health/social care systems; and understand change-process dynamics including barriers and facilitators to implementing PM+. An ethnographic method will be adopted including observation of PM+ implementation alongside semi-structured interviews and focus group discussions with key stakeholder groups such as lay therapists, Wellbeing Mentors, PM+ participants, representatives from NGOs working with AS&R communities, health professionals and commissioners from Liverpool City Region. Heterogeneity within the population will be considered and whether the intervention’s feasibility and effectiveness may differ by demography or asylum status, and how this may influence the choice of target population for our proposed definitive trial.

Analysis will be based on narrative synthesis, combining data tabulation and narrative techniques. This will involve iterative review and refinement in order to reach agreement on a set of general propositions in relation to the data. The perspectives of Normalisation Process Theory [47, 48] will be used to assess the potential for implementing a full RCT, focussing on the progression criteria set out above.

### Discontinuation and withdrawal

In consenting to the trial, participants agree to all trial activities including administration of trial intervention and follow-up assessments/visits and data collection. Every effort will be made to facilitate the completion of these for every recruited participant. If it is not possible to complete these activities (or it is deemed inappropriate) the reasons why should be documented.

Participants may discontinue the study intervention for reasons including, but not limited to:
Participant-led, i.e. request by the participantResearcher/clinician/lay therapist-led:
Any change in the participant’s condition that justifies the discontinuation of the intervention in the researcher/clinician/lay therapist’s opinionReasons of non-adherence or non-compliance with study intervention or other trial procedures, e.g. unable to complete course of PM+Participant meets an exclusion criterion (either newly developed or not previously recognised)

Discontinuation from PM+ does not mean discontinuation of the study altogether, and the remaining study procedures, i.e. 13- and 26-week follow-up visits and data collection, and process evaluation, will be completed as indicated in the protocol (unless consent is specifically withdrawn).

Participants are free to withdraw from follow-up at any time without providing a reason, though a reason should be recorded if one is given. Those who wish to withdraw from further follow-up will have the data collected up to the point of that withdrawal included in the analyses. The participant will not contribute further data to the study and the LCTC will be informed, via email to the LCTC and via completion of a Withdrawal CRF to be returned to the LCTC within 24 h. Death of a participant would be recorded on a Withdrawal CRF and a Death CRF.

For participants moving from the area, every effort will be made for the participant to be followed up and to complete their remaining study appointment(s) remotely.

A participant will be considered lost to follow-up if they fail to return for any scheduled visits and are not contactable by the site research team. If a participant fails to attend/facilitate a required study visit the following actions must be taken:
The researcher will attempt to contact the participant and reschedule the missed visit (be conscious of acceptable windows for collecting valid data) and advise the participant on the importance of maintaining the assigned visit scheduleBefore a participant is deemed to be lost to follow-up, the research team will make reasonable effort to regain contact with the participantIf the participant continues to be unreachable they should be considered withdrawn from the study with a primary reason of lost to follow-up and this should be recorded on the Withdrawal CRF

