**Health economics:**		
Use of services and supports from NHS, social care and voluntary sectors	Adapted Client Service Receipt Inventory (CSRI) [37]	Baseline, 13-week and 26-week follow-up assessments

HADS is a well-established, 14-item scale consisting of 2 subscales: HADS-A (anxiety; 7 items; possible score range, 0–21) and HADS-D (depression; 7 items; possible score range, 0–21). Higher scores indicate more anxiety and/or depression. HADS has been widely used across cultures; it is sensitive to change over time and has good internal consistency, reliability and validity [38]WHO-5 is validated in international studies for both clinical and psychometric properties and is available in many languagesWHODAS is applicable across all health states including mental disorders. It has good validity in terms of internal consistency, test-retest reliability, and agreement with other measures of disability across countriesPSYCHLOPS has internal consistency, convergent validity with measures of emotional distress, and is sensitive to change. It covers 3 domains: problems (2 questions), functioning (1 question) and well-being (1 question)PCL-5 has good psychometric properties for diagnostic accuracy and internal consistencyPHQ-9 is based on DSM-IV depression diagnostic criteria. Total severity score ranges from 0 to 27, with 10 as conventional cut-off to diagnose depressive disorderThe CSRI has been adapted for the PROSPER trial to include health, social care and voluntary services with the potential to be used by asylum seekers and refugees

Other elements of PROSPER Pilot will be assessed and used to inform the feasibility of conducting a full trial, as specified in Table 2.

**Table 2 Tab2:** PROSPER feasibility measures

Objective	Outcome measure	Time point(s) of evaluation
To assess the feasibility of the proposed procedures for recruiting distressed AS&Rs as study participants	Number of asylum seekers and refugees (AS&Rs) recruited	Baseline
To assess feasibility of randomisation	Successful randomisation of participants	Baseline (randomisation)
To assess the feasibility of retaining study participants through to trial completion	Number of study participants in the trial (assessed in individual arms)	26 weeks
To assess the acceptability and utility of specified primary and secondary outcome measures	Completion of study measures and estimation of between group differences Evaluation of outcome measures	Baseline, 13 weeks, 26 weeks

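### A participant still unreachable after a missed 13-week visit is classed as withdrawn while the 26-week visit is due, which may lose 26-week data and understate 26-week retention

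*Protocol article*

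**What the plan says.** All of the following is in the protocol article.

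- **Definition** (Discontinuation and withdrawal): "A participant will be considered lost to follow-up if they fail to return for any scheduled visits and are not contactable".
- **Trigger** (same section): "If a participant fails to attend/facilitate a required study visit the following actions must be taken". One missed visit is enough to start the procedure.
- **Steps before the label** (same section): "The researcher will attempt to contact the participant and reschedule the missed visit". The team must then make reasonable efforts to regain contact. No number of attempts and no time limit is given.
- **Label** (same section): if "the participant continues to be unreachable they should be considered withdrawn from the study with a primary reason of lost to follow-up", and this goes on the Withdrawal CRF.
- **Visits** (Assessments and follow-up, Table 4): 13 ± 2 and 26 ± 2 weeks. Telephone and then post are the fallbacks when a face-to-face visit cannot be arranged.
- **Retention** (Outcome measures, Table 2): the objective is "To assess the feasibility of retaining study participants through to trial completion". It is measured as the number of participants in the trial, by arm, at 26 weeks.
- **Use of retention**: the sample size rests on it (Statistical considerations: 35 per arm, 80% expected, ± 13%). It is also a progression criterion (Table 3: Go at 70% or more, Amend at 50–69%, Stop below 50%).

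**The concern.** At 13 weeks the rule can apply while one of the two follow-up visits is still to come. The participant has not withdrawn consent, but the status assigned is withdrawal from the study. A person with that status is hard to count as being in the trial at 26 weeks, and staff have no instruction to try again. Temporary loss of contact is plausible here: Assessments and follow-up notes that week 13 may often coincide with Home Office decisions.

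The rule also fits poorly with the rest of its own section. That section commits the team to making every effort to complete follow-up for everyone recruited. It keeps people who stop PM+ in both follow-up visits unless they specifically withdraw consent. Someone who declines the intervention therefore stays in follow-up, while someone merely out of contact is classed as withdrawn.

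At stake are 26-week outcome data that might have been collected and the retention figure that the full trial would be planned on. The article also plans to judge the feasibility of the 13- and 26-week time points by attrition (Process evaluation and feasibility assessment). If non-contact at 13 weeks is carried forward by status, attrition at 26 weeks is not measured in its own right.

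**Working it through.** **1. The plan's own precision figure.** Inputs from Statistical considerations: p = 0.80, n = 35 per arm, 95% confidence. The half-width is 1.96 × √(0.80 × 0.20 / 35) = 0.1325, which gives 66.7% to 93.3%. This agrees with the stated ± 13% (67 to 93%). The point raised here does not affect that figure.

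**2. Size of the possible shortfall.** Let m be the share of an arm unreachable at 13 weeks, and r the share of those who could be reached at 26 weeks. If nobody classed as withdrawn at 13 weeks is approached again, recorded 26-week retention falls below achievable retention by m × r. The shortfall cannot be negative, and it is zero when r = 0. The document gives neither m nor r, so the values below are assumptions. Achievable retention is set at the protocol's 80%. Go in one arm needs at least 25 of 35, because 0.70 × 35 = 24.5. P(Go) is the binomial probability of 25 or more out of 35 at the recorded rate.

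| m | r | Shortfall (points) | Recorded retention | P(Go), one arm |
|---|---|---|---|---|
| any | 0 | 0 | 80.0% | 92.5% |
| 5% | 10% | 0.5 | 79.5% | 91.4% |
| 10% | 25% | 2.5 | 77.5% | 85.6% |
| 10% | 50% | 5.0 | 75.0% | 75.8% |
| 20% | 25% | 5.0 | 75.0% | 75.8% |
| 20% | 50% | 10.0 | 70.0% | 51.0% |
| 25% | 50% | 12.5 | 67.5% | 38.4% |

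**3. In numbers of people.** Start from 28/35 = 80% in one arm:

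- three such people leave 25/35 = 71.4%, still Go;
- four leave 24/35 = 68.6%, which is Amend.

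Four of 35 is 11.4 points. Reaching that needs, for example, m = 25% with r = 46% (0.114 / 0.25), or m = 20% with r = 57% (0.114 / 0.20). If the criterion is applied to all 105 participants, Go needs at least 74 (0.70 × 105 = 73.5). Starting from 84 retained, 11 such people would be needed to fall below it.

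**The case against.** Much can be said for the rule, and a reader might infer more from it than the document supports.

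- **Not being reached once does not make someone withdrawn.** Rescheduling and further efforts come first, telephone and post are available, and those who move away are to be followed remotely. With no deadline set, efforts could run on towards week 26. This stands, but these safeguards come before the label and do not reopen follow-up after it.
- **A reader might infer that dropout is irreversible by rule.** The document does not say so. Nothing bars a 26-week approach. The sentence "The participant will not contribute further data to the study" is written about people who wish to withdraw from follow-up. The definition's reference to any scheduled visits could also mean all of them. If all was meant, however, the single-visit trigger conflicts with it and needs correcting.
- **A reader might infer that loss of contact cannot be told from refusal.** It can, because the Withdrawal CRF carries lost to follow-up as the primary reason.
- **A reader might infer that the control arm is hit hardest.** The document does not establish this. Control participants are encouraged to meet weekly for five weeks to match contact (Control arm), PM+ itself lasts only five weekly sessions, and retention is assessed by arm.
- **Size.** From the protocol's own 80%, even m = 20% and r = 50% give an expected 70%, which still meets Go. A downward bias is possible but not demonstrated.
- **Same rule later.** If the full trial kept this rule, the pilot would estimate retention under it correctly. The understatement is relative to what continued contact could achieve.
- **Condensed article.** Numbers of contact attempts may well be in the full protocol. The point does not depend on them, because the article itself states the status rule.

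**Conclusion.** The point holds as a defect of wording that can affect a key quantity. As written, a participant untraceable after a missed 13-week visit is classed as withdrawn with a visit still due and consent intact. This can only lower recorded 26-week retention and data, or leave them unchanged. The size is m × r, and the document gives neither term. Over the assumed range (m 5–25%, r 0–50%) it runs from 0 to 12.5 points. Moving an arm from 80% to Amend takes four such people out of 35, a fairly demanding combination of m and r. All of these figures assume full recruitment of 35 per arm and no renewed contact after the label. Confidence is high that the wording needs correcting and low on how much difference it would make. The change is worth making because retention is what the pilot is sized to estimate and the remedy is cheap.

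**What to change.** Amend Discontinuation and withdrawal, and the matching CRF guidance, as follows:

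1. A participant who cannot be reached for the 13-week visit is recorded as having missed that visit, stays in the trial, and is approached again for the 26-week visit unless consent is withdrawn.
2. Lost to follow-up is assigned only when the 26-week window closes.
3. Withdrawn is reserved for withdrawal of consent.
4. In Table 2, 26-week retention is counted as participants with 26-week data obtained, by arm.

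The cost is a change of wording and a few extra contact attempts by the existing researcher. Sample size and visit schedule do not change.
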